### Randomization

#### Sequence generation and allocation concealment and implementation

The allocation sequence will be generated using the random number function in Excel. The allocation sequence will be generated by an investigator not involved in assessment and treatment codes placed sequentially into sealed opaque envelopes. Baseline assessment will be conducted prior to group allocation by an investigator blind to the allocation sequence. Following assessment, participants will be issued a sealed envelope containing their group allocation and those in tai chi group scheduled to attend their first class within one week.

The tai chi intervention includes a series of movements to be taught sequentially and is taught in a group format. For reasons of practicality, the randomization code was developed using a computer random number generator in a block size of 8. This allows us to allocate 4 subjects to the tai chi class, and 4 to control for each block. This assists scheduling of tai chi classes which are held in groups.

#### Blinding

Participants will not be blinded to treatment as the control group is not receiving any intervention in addition to their usual care. The investigator responsible for delivery of treatment will be blinded to allocation sequence and will become unblinded as participants enter treatment group. The investigators responsible for the monitoring of treatment and attending to clinical issues that arise during the conduct of the study will be unblinded. Assessment is self-report questionnaire completed by participants which precludes blinding of assessment. The investigators responsible for data analysis will be blinded to treatment allocation for the duration of trial.

### Timeline

Timeline and flow from screening through randomization and follow-up assessments are shown in Table 2. Participants who successfully meet the inclusion criteria will be asked to attend an initial group session to complete the baseline assessment including a series of questionnaires. After all outcome measures are completed and checked by the blinded assessor for any missing or incomplete data, the participants will be randomized into the intervention or control group. The blinded assessor will score and enter the outcome measure data into an SPSS spreadsheet. The tai chi instructor will organize the intervention group to begin their first tai chi session within one week of randomization. The participants in the tai chi intervention group will continue to attend tai chi sessions 2 times per week for 8 weeks, followed by 1 time per week for 2 weeks. The control group will be asked to continue with their usual health care for the following 10 weeks and given the opportunity to participate in a tai chi program identical to the one in the intervention group, upon completion of the follow-up assessment. During the 10 week intervention both groups will receive a bi-weekly questionnaire via email. The questionnaire collects data on the health care services accessed by the participant in the prior 2 weeks. Upon completion of the 10 week intervention, all participants will attend the follow-up assessment in a group format. To maximize attendance at the follow-up assessment each participant will be contacted by phone, email or a sms text to confirm attendance 1 week prior to follow-up assessment. An additional reminder will be made 1 day prior to follow-up assessment. The outcome data will be scored and entered into an SPSS spreadsheet within 3 days by one of the blinded investigators.

**Table 2 T2:** Participant flow and timetable from screening to follow-up assessment

**Timeline**	**Action**	
Week 0	Telephone screen conducted by one of the investigators	receive patient information statement verbal consent complete telephone screening questionnaire to determine eligibility eligible individuals are invited to attend baseline assessment conducted in groups of 8 individuals
Week 1	Baseline Assessment administered by blinded assessor	sign patient informed consent complete demographic data complete baseline questionnaires
	Randomization	*generation*: using sealed opaque envelopes containing allocation sequence generated by a computer random number function *allocation*: the unblinded tai chi instructor will assign participants to one of two groups the tai chi intervention group or the wait-list control group
Week 2 – 11	Intervention conducted by un-blinded investigator	*Tai chi group*: 2 × 40 min group sessions/week for 8 weeks 1 × 40 min group session/week for 2 weeks
		*Wait-list control group*: Continue with pre-established usual health care After follow-up assessment is complete, participant can join in tai chi program identical to that of intervention
	Assessments during intervention administered via email by blinded assessor	Both groups will receive a bi-weekly questionnaire asking them to list the health care services they have used for their back symptoms
Week 12	Follow-up Assessment administered by blinded assessor	administered by blinded assessor complete follow-up questionnaires after assessment, blinded assessor will leave and tai chi instructor will hand-out certificates of completion to tai chi group and schedule wait-list control group for tai chi program

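### Table 2 gives allocation to the unblinded tai chi instructor under a fixed block of 8, which fits poorly with the Blinding section and can make later codes predictable

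*Protocol article*

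**What the plan says.** The protocol article describes allocation in three places.

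- **Randomization.** The sequence is "generated by an investigator not involved in assessment and treatment codes placed sequentially into sealed opaque envelopes". On issue, the text says: "Following assessment, participants will be issued a sealed envelope containing their group allocation". This is in the passive and names no issuer. On blocking, "the randomization code was developed using a computer random number generator in a block size of 8", and "This allows us to allocate 4 subjects to the tai chi class, and 4 to control for each block".
- **Blinding.** "The investigator responsible for delivery of treatment will be blinded to allocation sequence and will become unblinded as participants enter treatment group".
- **Timeline, Table 2.** The randomization row repeats the sealed opaque envelopes and then says "the unblinded tai chi instructor will assign participants to one of two groups". The next row reads "Intervention conducted by un-blinded investigator".

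The Timeline section and Table 2 also plan baseline assessment in sessions of eight people, the same number as a block, and place randomization after the questionnaires have been completed and checked.

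**The concern.** Table 2 is the only place that names the person who allocates. It names the treatment provider and calls that person unblinded at the randomization step, when nobody in the new block has yet entered treatment. The Blinding section describes the same role as still blind to the sequence at that point.

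The wording matters because of what the instructor knows. The instructor takes attendance at every class, and four class members from a session of eight make the block size plain. Sealed envelopes hide the code inside, but they do not prevent deduction from earlier codes in a fixed block. Concealment should keep the matching of people to envelopes away from someone with that knowledge.

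The outcomes are self-reported by participants who know their group, against a wait-list control. Allocation concealment is therefore one of the few protections against bias that this design can keep. If more motivated or more expectant participants were matched to tai chi codes, the comparison would tilt towards tai chi.

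**Working it through.** **The passages side by side**

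1. Who makes the sequence: an investigator not involved in assessment (Randomization).
2. Who hands out the envelopes: not named in Randomization; the instructor in Table 2.
3. What the provider knows at that moment: not the sequence (Blinding); described only as unblinded (Table 2).

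These can be read together if unblinded in Table 2 is a role label: the instructor knows past allocations but not the list. The remaining question is how much of the list past allocations reveal.

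**Inputs**

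- Block size 8 with 4 per arm, so m = 4 (Randomization).
- 160 participants (Sample Size), so 160 / 8 = 20 blocks.
- Assumption A: the allocator knows the block size. The documents do not say so, but class and session sizes make it evident.
- Assumption B: envelopes are opened one at a time, and each result is seen before the next person is matched to an envelope. The documents neither state nor exclude this.

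The plan gives no figure for predictability, so there is none to reproduce.

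**Codes known with certainty (A and B)**

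A code is certain once one arm of the block is used up, so the certain codes are the final run of identical codes. Each tai chi code falls after all four control codes with probability 1/5, which gives 4 × 1/5 = 0.8 expected. The same holds for control codes after the last tai chi code. The total is 2m/(m+1) = 8/5 = 1.6 of 8, or 20%. Over 20 blocks this is 20 × 1.6 = 32 of 160.

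**Codes guessed correctly (A and B)**

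The best strategy is to guess the arm with more codes left and to toss a coin at ties. Expected correct guesses are m + 2^(2m−1)/C(2m, m) − 1/2 = 4 + 128/70 − 0.5 = 5.33 of 8, or 66.6%. Over 20 blocks this is about 107 of 160, against 80 by chance. Enumeration of all 70 possible 4:4 sequences gives the same 1.6 and 5.33.

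**How this depends on the session**

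- *Eight attend and all envelopes are matched to people while sealed.* Nothing usable is predictable.
- *Eight attend and envelopes are opened one by one.* The figures above apply. All eight are already enrolled, so only who in the room gets which envelope could be affected.
- *Seven attend and the block carries over.* With seven codes open, the eighth is known before the next session begins.
- *Six attend and the block carries over.* The two remaining codes are identical with probability 2 × (4/8 × 3/7) = 3/7, and both are then known in advance. Otherwise one of each remains, and the second is known once the first is opened.

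The documents do not say how often sessions fall short, so the share of participants affected cannot be estimated.

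**The case against.** The strongest reply is that the passages are compatible and the safeguards sound. A class teacher can know past allocations and remain blind to the upcoming sequence, which is what the Blinding section describes. Table 2 uses the same label for whoever conducts the intervention, so it may only mark a role. To assign may mean no more than handing over the next sealed envelope. The sequence is made by someone not involved in assessment, envelopes are sequential, sealed and opaque, and allocation follows baseline. When a session of eight fills, enrolment cannot be steered. Envelope custody and short sessions are operational details that an article may leave to the full protocol.

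Most of this stands, and it rules out several stronger readings that a reader might infer:

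- *The instructor knows the sequence, or concealment has failed.* No passage says that the instructor generates, holds or sees it.
- *The instructor may choose who gets which envelope.* No passage grants that discretion; the text only fails to exclude it.
- *About 32 of 160 allocations are exposed.* That figure needs both assumptions in every block.
- *No analysis could help.* The planned model uses baseline outcome values through its time terms, and treatment expectation is listed among the baseline predictors. Imbalance on these measures would be visible and partly adjustable, although selection on unmeasured traits would not be cured.

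The reply does not remove the point that Table 2 gives allocation to the treatment provider. This is stated content, not omitted detail, and reading the label as a role does not take away the instructor's knowledge of past codes.

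**Conclusion.** The point holds as a conditional weakness in allocation concealment, together with wording that needs reconciling. Table 2 has the person who knows all earlier allocations carry out assignment under a fixed 4:4 block of 8, which sits poorly with the Blinding section, and the Randomization section does not settle who issues envelopes.

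The size is a ceiling: on average at most about 1.6 of 8 codes certain and 67% guessed correctly, if envelopes are opened sequentially and the block size is known. With full sessions and envelopes matched while sealed, it falls to nothing usable. These figures measure predictability and do not forecast bias. Sample size and power are unaffected. The change should be made because it is specific and nearly free; confidence is medium because the risk depends on procedures that the article does not fix.

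**What to change.** Change the randomization row of Table 2 as follows.

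1. Once all baseline questionnaires in the session are checked, someone other than the instructor, such as the blinded assessor already present, writes participant IDs in a fixed order on the sequentially numbered, still sealed envelopes.
2. That person leaves before any envelope is opened, so that the assessor stays blind. Table 2 already has the assessor leave at the week 12 session before the instructor deals with each group.
3. The instructor receives the class list only after the envelopes have been opened.

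Reconcile the Randomization and Blinding sections with this: name who issues the envelopes, and state that this person does not know the sequence. Matching in a fixed order while sealed also covers the envelope step when a short session carries a block over.

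The cost is a small change in session procedure and a few words of text. Block size, class size, sample size and analysis stay as they are.

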### Statistical Methods

#### Primary analysis: treatment efficacy

Statistical analysis of primary and secondary outcomes will be based on the intention to treat principle. The effect of intervention on bothersomeness of pain, pain intensity, function, disability and global perceived effect will be determined using linear mixed models (random intercepts and fixed coefficients) which incorporate terms for treatment, time and the treatment by time interactions. The coefficients of the treatment by time interactions provided estimates of the effects of the tai chi intervention. A treatment effect size will be calculated for each of the follow-up time points and, if there is a statistically significant treatment effect at any time point, we will also calculate number needed to treat (NNT) to achieve pain recovery (pain < 1 out of 10: [43] and 95% confidence intervals.

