### Sample Size

We have designed the study to detect a clinically important difference of 1.5 units on the 0–10 bothersomeness scale (estimate for SD = 2.35), 1 unit on the 0–10 pain numerical rating scale (estimate for SD = 2), 1 unit on the 0–10 patient specific functional scale (estimate for SD = 1.8); 1 unit on the 0–10 Global Perceived Effect Scale (estimate for SD = 1.65), 4 units on the 24 item Roland Morris Disability Questionnaire (estimate for SD = 4.9). We have taken the SD estimates from trials that recruited a similar patient cohort [3,29,40]. Given these considerations we have chosen to design the study to detect an effect size of 0.5 SD. Based upon the results of a similar trial by our group [3] we have allowed for 15% non-compliance with treatment, 15% loss to follow-up, and assumed a correlation between baseline and change scores of outcomes of 0.5. Taking these factors into account with specifications of alpha = 0.05, power = 0.80 a sample size of 77 participants per group is required to detect an effect size of 0.50 SD [41]. Accordingly we will recruit 80 participants per group or 160 participants in total to allow for treatment in blocks of 8. Blocks of 8 allow us to randomize 4 subjects at the one time to the Tai Chi group and so have a sufficiently large class.

As a secondary analysis we will evaluate predictors of response to treatment. We estimate that it would require ~640 subjects to detect an interaction effect of the same magnitude as the main effect. We do not have the resources for such a study. Accordingly we acknowledge that we may miss an interaction effect in our analyses. Brookes and colleague's simulations demonstrate that when testing for effect modification, trials have the same power to detect an interaction effect that is twice the size of the main effect [42].

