## Discussion

This study will evaluate the effects of a 10-week tai chi exercise program on people with long-term low back pain. The study is adequately powered to detect change in the primary and secondary outcomes that include bothersomeness of back symptoms, self-reported disability and physical function and global perceived effect of treatment. The focus of this study is to determine the efficacy of tai chi as an intervention for long-term low back pain; it aims to provide both health care providers and patients with evidence-based advice for treatment planning. To our knowledge this is the largest study specifically designed to examine the effect of tai chi on low back symptoms in people with long-term low back pain.

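### The sample size credits a baseline adjustment that the stated primary model does not make, so power at 0.5 SD is about 70%, not 80%

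*Protocol article*

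**What the plan says.** The Sample Size section of the protocol article sets its target generically: "we have chosen to design the study to detect an effect size of 0.5 SD". It allows for "15% non-compliance with treatment, 15% loss to follow-up", and the authors "assumed a correlation between baseline and change scores of outcomes of 0.5". With "specifications of alpha = 0.05, power = 0.80", it concludes that "a sample size of 77 participants per group is required to detect an effect size of 0.50 SD", and then that "we will recruit 80 participants per group or 160 participants in total".

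The section on the primary analysis (Statistical Methods) specifies "linear mixed models (random intercepts and fixed coefficients) which incorporate terms for treatment, time and the treatment by time interactions" and states that the treatment-by-time coefficients are the estimates of the tai chi effect. The Outcomes section and Table 2 give one baseline and one follow-up at 10 weeks. A baseline score enters as a regressor only in the secondary analysis of predictors of response.

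The Discussion states: "The study is adequately powered to detect change in the primary and secondary outcomes".

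**The concern.** The assumed correlation of 0.5 is there to reduce the required number. A correlation r with the baseline score removes a fraction r² of the variance when the analysis conditions on that score. The stated model does not condition on it. Baseline is one of two repeated responses, and the treatment main effect leaves the two arms free to have different baseline means. With a single follow-up, the interaction is then simply the difference in mean change.

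If so, the stated 80% power belongs to a different analysis from the one planned, and the planned estimator is less precise than it could be with the same data. The same imprecision shows as regression to the mean: a chance difference between arms at baseline passes into the estimated effect.

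**Working it through.** **Inputs (Sample Size section).** Effect 0.5 SD; alpha 0.05, taken as two-sided because sidedness is not stated; power 0.80; non-compliance 15%, read as shrinking the effect to 0.85 of its value; loss 15%; correlation 0.5; 80 recruited per arm.

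**Step 1: reproduce 77.**
- Two means, no allowances: 2 × (1.960 + 0.842)² / 0.5² = 62.8 per arm.
- Non-compliance: 62.8 / 0.85² = 86.9.
- Baseline adjustment: 86.9 × (1 − 0.5²) = 86.9 × 0.75 = 65.2.
- Loss: 65.2 / 0.85 = 76.7, so **77**, as stated.
- Without the 0.75: 86.9 / 0.85 = 102.2, so **103**.

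Other combinations do not give 77: 0.75/0.85² gives 66, 1/0.85² gives 87, 1/0.85 gives 74, and a one-sided test with every allowance gives 61. Applying loss as × 1.15 gives 75, which is close, but it also needs the 0.75.

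**Step 2: what the stated model estimates.** With two visits and complete data, the treatment-by-time coefficient equals the difference in mean change. A numerical check on one simulated data set gave −0.4836 with standard error 0.171 by both routes. With equal SDs at the two visits and baseline–follow-up correlation r, the variance of change is 2(1 − r) SD², which is 1.0 SD² at r = 0.5. ANCOVA leaves (1 − r²) SD² = 0.75 SD².

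The two readings of the 0.5 agree. With equal SDs the baseline–change correlation is −√((1 − r)/2), which is −0.5 at r = 0.5. If instead the SD is taken as that of the change score and the 0.5 is read literally as baseline with change, the unadjusted variance is 1.0 and the adjusted variance 0.75.

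**Step 3: power at 0.5 SD with 80 per arm.** Completers: 80 × 0.85 = 68 per arm. Diluted effect: 0.5 × 0.85 = 0.425 SD.
- With baseline adjustment: 0.425 / √(2 × 0.75/68) = 2.86; power = Φ(2.86 − 1.96) = **81.6%**.
- Stated model: 0.425 / √(2/68) = 2.48; power = Φ(2.48 − 1.96) = **69.8%**.
- Stated model, also using the baselines of those lost: variance 2 × (0.75/68 + 0.25/80) = 0.0283; 0.425/√0.0283 = 2.53; power **71.4%**.

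A simulation of 20,000 trials with 68 completers per arm gave 80.4% for ANCOVA and 69.1% for change.

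**Step 4: detectable effect at 80% power, 80 per arm.** Stated model: 2.802 × √(2/(80 × 0.85³)) = 0.57 SD. With adjustment: 0.565 × √0.75 = 0.49 SD.

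**Step 5: the article's own target differences, 80 per arm.**

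| Outcome | Difference / SD | Stated model | Baseline-adjusted |
|---|---|---|---|
| Bothersomeness (primary) | 1.5/2.35 = 0.64 | 89% | 95% |
| Pain rating | 1/2 = 0.50 | 70% | 82% |
| Patient specific function | 1/1.8 = 0.56 | 79% | 89% |
| Global perceived effect | 1/1.65 = 0.61 | 85% | 93% |
| Roland Morris | 4/4.9 = 0.82 | 98% | over 99% |

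Global perceived effect is a rating of change. If it has no baseline score, its adjusted figure does not apply.

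**The case against.** The strongest reply is that little of practical importance fails. The primary outcome has 89% power at its own stated difference. Of the five targets in the Sample Size section, only pain intensity falls well short of 80%. Function misses by about a point, and pain intensity does not appear in the article's list of specific outcome measures. The change-score contrast is unbiased in a randomised trial and keeps its type I error, and the effect of chance baseline imbalance is already counted in the larger variance, so it is not a second harm. All of this stands and limits the consequence. It does not rescue the 80% claimed at 0.5 SD, which is the effect the trial says it was designed to detect.

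Second, the agreement between the two readings of the 0.5 depends on equal SDs. If 0.5 is the baseline–follow-up correlation and the entry criterion of at least moderate pain or limitation narrows the baseline spread, the loss is smaller. With a baseline SD of 0.8 of the follow-up SD, the change variance is 1 + 0.64 − 0.8 = 0.84 and power is 77%. At 0.7 it is 1 + 0.49 − 0.7 = 0.79 and power is 80%. The article gives no separate SDs, so these ratios are assumptions, and its literal wording (baseline with change) supports the factor of 1.0.

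Third, the article is condensed, and an unseen analysis plan might add a baseline covariate. But the article fixes both the model terms and the coefficient to be reported. With one follow-up, a treatment-by-time term exists only if baseline is a level of time, so a later document would have to change the stated model.

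**Conclusion.** The concern holds. The sample size and the primary model contradict each other: 77 per group needs the 0.75 factor, and the stated interaction estimate does not deliver it. At 0.5 SD with 80 per arm, power is about 70% (71% if baselines of those lost contribute), against 82% by formula and 80% by simulation with adjustment. The effect detectable with 80% power is 0.57 SD rather than 0.49 SD.

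The primary outcome remains above 80% at its 1.5-point target. What is wrong is the 80% statement at 0.5 SD and, with it, the Discussion's general claim of adequate power, which is clearly short for pain intensity and marginally short for patient specific function.

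The result assumes a two-sided test, non-compliance acting as a 15% dilution, 15% loss in each arm and, for the baseline–follow-up reading of the correlation, equal SDs at the two visits.

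**What to change.** Before analysis, change the primary model so that it uses the baseline score as the sample size assumes. There are two routes, and one should be named:

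- Keep the mixed model but drop the treatment main effect, so that the arms share a common baseline mean, and report the treatment effect at 10 weeks.
- Use ANCOVA of the 10-week score on treatment and the baseline score.

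The two give closely similar answers but are not identical when participants are lost or the variances differ between visits. Apply the choice to every outcome that has a baseline value. This restores about 82% power at 0.5 SD with the planned 80 per arm.

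If the present model is kept, the Sample Size section should give power of about 70% at 0.5 SD, and the Discussion's claim should be qualified to match.

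The cost is one sentence of analysis wording. The baseline scores are already collected, and no further participants are needed.
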